### Plans to give access to the full protocol, participant-level data and statistical code {31c}

To guarantee participant anonymity, the data set on participant level will not be publicly available. The data and statistical code supporting the findings of the final study report will be available on reasonable request.

## Oversight and monitoring

### Composition of the coordinating centre and trial steering committee {5d}

The research teams consist of the principal investigator (CP), a clinical psychologist in training (MK), two senior researchers (CdR, AD), a professor of an affiliated university (BE) and a research assistant (MV). The principal investigator is responsible for daily monitoring, for contact with the independent researcher performing the randomization, and for all contacts with participating practitioners. Assessments will be coordinated by the second investigator (MK) and the research assistant to guarantee blindness to treatment condition. The research team bimonthly evaluates the progress of the study. The local principal investigator of participating institution GGZ Delfland (MB) was involved in the design of the study and will be involved in the practical implementation of the study and in the reporting of the results.

For participants, an independent expert is available for questions about the trial.

### Composition of the data monitoring committee, its role and reporting structure {21a}

Collection, storage and processing of the data will be performed by the research team, with the assistance of a research assistant and master degree students. Because of the low risks involved in this study, no official data monitoring committee will be formed. To promote data quality, regular data monitoring will be done by an independent peer auditor, not involved in the study. This auditor will randomly check the research file on inclusion pace, drop-outs and general presence of completeness of the data.

### Adverse event reporting and harms {22}

Adverse events are defined as any undesirable experiences occurring to a subject during the study, whether or not considered related to the intervention. During EMDR treatment, the number of adverse events such as symptom exacerbation, crisis contacts and self-injurious or suicidal behaviour will be recorded each session. All by participants, assessors or practitioners reported or observed adverse events will be recorded in the sessions forms, which are stored on a secured storage.

A serious adverse event (SAE) is defined—conform the guidelines of the Dutch Central Committee on Research Involving Human Subjects (CCMO)—as any untoward medical occurrence or effect that results in death, is life threatening (at the time of the event), requires hospitalization or prolongation of existing inpatients’ hospitalization or results in persistent or significant disability or incapacity.

The study group will report all SAEs through the web portal ToetsingOnline to the accredited Medical Ethical Committee, without undue delay after obtaining knowledge of the events (a period of 8 days of first knowledge to complete the initial preliminary report for SAEs that result in death or are life threatening; a period of maximum 15 days for all other SAEs).

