### Trial design {8}

This study is designed as a randomized, controlled, single-blinded two-center superiority trial with two parallel groups. All patients meeting the inclusion criteria are asked for written informed consent to participate in the intervention study. For consenting participants, baseline measures (T0) are completed subsequently. Randomization will be performed as block randomization with a 1:1 allocation stratified per treatment location. An independent researcher will conduct randomized allocation by using the SPSS function to produce random numbers. Hence, the main researcher will be blind to the randomization process. Randomization will take place in blocks of 10 participants. After completing the baseline assessments (T0), participants will be informed in which group they have been randomized. Assessments (see Fig. 1) are scheduled pre-treatment (T0), post-treatment (T1), and at 3-month (T2) and at 6-month (T3) follow-up. Assessment will be done by a team of independent assessors (i.e. trained clinicians and supervised master level students) who are blind for condition. Participants in the waiting list condition are offered EMDR treatment after T1 and are subsequently assessed post-treatment and at 3 and 6 months follow-up (see Fig. 1). For participants in the waiting list condition, T1 will be labelled as T0WL when they enter treatment (*t*_*1*_ = *t*_*0-wl*_).

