#### EMDR therapy

The Dutch version of the standard EMDR protocol with age-specific adaptations for children and adolescents [36] will be used. This procedure includes eight phases: history taking, preparation, assessment, desensitization, installation, body scan, closure and re-evaluation. Before start of the treatment, a case conceptualization is made to guide the sessions. Memories are placed in a hierarchy based on the subjective units of disturbance (SUD), and will be treated subsequently from high to low SUD. If all depression-related target memories from the case conceptualization can be retrieved without emotional disturbance (i.e. SUD related to the memory is reduced to zero) in less than six sessions, a participant will be classified as an early completer.

Treatment consists of a maximum of six weekly 60-min individual treatment sessions. Each session will be followed by a 15-min meeting with the therapist, adolescent and one or both parents. The content of this meeting is discussed beforehand with the adolescent and comprises any one of the following elements: (1) a content outline of the session, (2) parents’ view on the course of symptoms in the week before the session and (3) the need and possibilities for emotional support of the adolescent after the session. During EMDR treatment, the number of adverse events such as symptoms exacerbation, crisis contacts and self-injurious or suicidal behaviour, will be recorded each session.

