#### Waiting list

For participants in the waiting list condition, a therapist is available in case of crisis or sudden worsening of symptoms; a record will be made of such contacts.

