##### Structured interview for depression and comorbid disorders

The Schedule for Affective Disorders and Schizophrenia for School Age Children Present and Lifetime Version (K-SADS-PL-5) is a semi-structured diagnostic interview designed to assess current and lifetime diagnoses for affective, psychotic, anxiety, behavioural, substance abuse and eating disorders [40]. The clinician-based computer version of the K-SADS-PL-5 is used. For the purpose of the current study, questions about traumatic interpersonal experiences that have been identified as being connected to the onset of depressive episodes [25] (i.e. loss, separation and humiliation (being bullied/isolated/ignored), will be added to the K-SADS-PL-5 PTSD section.

The complete Youth Version is administered during pre-intervention assessment; at post-intervention and follow-up assessments, only the Depressive Disorders section, and the supplements for Suicidality and Sleep problems are administered.

All assessors are trained according to a programme consisting of observing live K-SADS COMP interviews and several supervised interviews. Each K-SADS COMP report will be reviewed and discussed by a supervisor. Moreover, all assessors attend 6-weekly intervision meetings.

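### Adverse event recording is scheduled only at EMDR sessions, so counts up to T1 would not be comparable between the arms

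*Protocol article*

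**What the plan says.** Adverse event reporting and harms {22} sets a wide definition: "Adverse events are defined as any undesirable experiences occurring to a subject during the study", related to the intervention or not. The schedule that follows is narrower: "During EMDR treatment, the number of adverse events such as symptom exacerbation, crisis contacts and self-injurious or suicidal behaviour will be recorded each session". The section EMDR therapy repeats it. For events that come to light in other ways the article adds: "All by participants, assessors or practitioners reported or observed adverse events will be recorded in the sessions forms". No other adverse event form is named.

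For the waiting list, the section Waiting list provides that "a therapist is available in case of crisis or sudden worsening of symptoms; a record will be made of such contacts". These participants have no EMDR sessions until later: "Participants in the waiting list condition are offered EMDR treatment after T1" (Trial design {8}).

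Two scheduled sources run alike in both arms. One is the K-SADS: "at post-intervention and follow-up assessments, only the Depressive Disorders section, and the supplements for Suicidality and Sleep problems are administered". The other is the set of child and parent questionnaires, sent online (Plans for assessment and collection of outcomes {18a}).

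**The concern.** The definition covers the whole study, while the stated schedule and the named form cover only the weeks of treatment. During the six-week wait, and after the last session in either arm, there is no session at which to record and no session form to record on.

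The waiting-list arm is offered EMDR after T1, so T0 to T1 is the only randomized comparison with an untreated group. That is also where recording is most unequal: one arm has a recording point every week, and the other relies on a contact being made or an event being mentioned or noticed. A crude comparison of counts would probably lean towards more events under EMDR. In follow-up, a low count could not be told apart from the absence of a scheduled recording.

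This matters in a sample of depressed adolescents. The eligibility criteria exclude a suicide attempt or serious self-injury only where it required hospitalization in the past month. Concomitant care is limited to stable medication, and there is no data monitoring committee.

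**Working it through.** The article gives no adverse event figure to reproduce, so the check counts recording occasions from the stated schedule.

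**Inputs**
- Sessions: "Treatment consists of a maximum of six weekly 60-min individual treatment sessions" (EMDR therapy), so at most 6. Early completers have fewer.
- Wait: 6 weeks without EMDR (Abstract, Methods; Trial design {8}).
- Arm size: 64 / 2 = 32 (Sample size {14}).
- Assessments: T1, T2 and T3. Waiting-list participants, once treated, "are subsequently assessed post-treatment and at 3 and 6 months follow-up" (Trial design {8}).
- Drop-out: at most 30% (Sample size {14}).

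**Scheduled general adverse event recordings**

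| Period | EMDR arm | Waiting-list arm |
|---|---|---|
| T0 to T1 | up to 6 each; 32 × 6 = 192 at most | 0 each; 32 × 0 = 0 |
| Waiting-list arm's own treatment, after T1 | not applicable | up to 6 each |
| After the last session | 0 | 0 |

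**What else reaches the waiting-list arm before or at T1, by the event types the article names**
- Crisis contact: recorded if it happens.
- Exacerbation: visible at T1 if still present. The CDI-2 asks about the past 2 weeks, so in a 6-week wait about 6 − 2 = 4 weeks lie outside its window.
- Suicidal behaviour: the K-SADS Suicidality supplement is given at T1 in both arms, but nothing says that a positive finding becomes an adverse event.
- Self-injury: the article does not say that the supplement covers it. Otherwise it depends on being reported or noticed.

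What remains is mainly events that have passed by T1 or that nobody discloses.

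**Look-back window for added items at T1**
- Counted from the last contact: about 1 week under EMDR (sessions are weekly) against about 6 weeks on the waiting list. This would rebuild the inequality.
- Counted from T0: about 6 weeks in both arms.

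**Size of the fix**
- EMDR arm: T1, T2, T3 = 3 per participant.
- Waiting-list arm: T1, own post-treatment, 3 months, 6 months = 4 per participant.
- Total: 32 × 3 + 32 × 4 = 96 + 128 = 224 item sets per informant at full retention. With child and parent both answering, 2 × 224 = 448.
- If the full 30% dropped out before T1 with no further measurements: 224 × 0.70 = 156.8, about 157 per informant.
- Like-for-like inquiries at T1: 32 against 32 participants at full retention.
- Longest recall: 26 weeks / 2 = 13 weeks, taking the follow-ups as 3 and 6 months after treatment.

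**The case against.** The strongest reply is that capture outside sessions is broader than the schedule suggests. Waiting-list crisis and worsening contacts are recorded. Depression and suicidality are assessed at T1 and follow-up in both arms by assessors blind to condition. Questionnaires go to adolescents and parents alike. The sentence on events reported or observed by others is not limited to the treatment weeks, and serious adverse events go to the ethics committee whenever they become known. All of this stands, and it narrows the gap. A reader might infer that harms on the waiting list go uncaptured; the article does not support that.

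A reader might also infer that EMDR participants are actively questioned every week. The text says that events are recorded each session, not that they are elicited. The contrast is therefore between scheduled recording points and none, and the degree of active inquiry is unknown.

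It can further be said that no hypothesis or statistical method compares adverse events between arms. That is correct, so no planned result is damaged. It does not make the collected counts suitable for a safety statement by arm.

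Finally, this is a condensed article, and Table 1, Fig. 1 and the case record forms are not shown. That is a real limit. The point nonetheless rests on a schedule and a form that the harms section does state, not on silence.

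**Conclusion.** The point holds in a limited form, and the change should be made. As written, the harms section gives up to 6 scheduled general recordings per EMDR participant against 0 per waiting-list participant before T1, and none in either arm after the last session. The 192 against 0 is a ceiling on recording occasions, not an estimate of missed events; the size of any bias cannot be calculated from the article. The events at risk of being missed are mainly transient or undisclosed ones.

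Adverse event counts up to T1 would not support a fair comparison between arms. The efficacy analyses are unaffected, and it would go too far to say that any planned analysis is invalid.

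Confidence is moderate. The conclusion assumes that the case record forms hold no general adverse event items at T1 or follow-up. If they do, only the wording of the section needs correcting.

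**What to change.** In Adverse event reporting and harms {22}:

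1. Add the same brief, condition-neutral items (exacerbation, crisis contact, self-injury, suicidal behaviour) to the existing online child and parent questionnaires at T1, T2 and T3, and at the waiting-list arm's own post-treatment and follow-up assessments. Include treatment drop-outs who continue measurements.
2. Fix the look-back to the previous scheduled assessment, which at T1 means T0 to T1 in both arms.
3. Have the answers read by staff not involved in the assessments. Using the online questionnaires keeps the items out of the blinded interview.
4. Use an adverse event form not tied to sessions, and record positive K-SADS suicidality findings as adverse events.
5. Base any comparison between arms on the T1 items only. Report session-recorded events separately, by period (waiting, treatment, follow-up) and by how they were found (session, assessment, spontaneous).

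The cost is four questions at 3 or 4 existing assessments per participant and one form, with no extra visit. The downsides are slightly longer questionnaires, recall of about 6 weeks at T1 and up to about 13 weeks at follow-up, and higher reported counts. A small unblinding risk remains; under Concealment mechanism {16b} an unblinded assessment must be repeated in full by another assessor. Inclusion was expected to end in April 2023, so items added late may reach only some participants. Reporting by period and by source remains possible at any time.

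### Non-serious adverse events are recorded at each EMDR session but, on the waiting list, only through contacts or unscheduled reports, so their counts over the 6-week randomised period are not ascertained alike

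*Protocol article*

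**What the plan says.** The section Adverse event reporting and harms {22} of the protocol article defines an adverse event broadly, as "any undesirable experiences occurring to a subject during the study, whether or not considered related to the intervention". That definition covers both arms and the whole study.

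The capture rules are narrower and differ by arm:

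- **EMDR.** The EMDR therapy section states: "During EMDR treatment, the number of adverse events such as symptoms exacerbation, crisis contacts and self-injurious or suicidal behaviour, will be recorded each session". The harms section repeats this. The number of occasions follows from the same section: "Treatment consists of a maximum of six weekly 60-min individual treatment sessions". Early completers have fewer.
- **Waiting list.** The Waiting list section says that "a therapist is available in case of crisis or sudden worsening of symptoms; a record will be made of such contacts". It sets out no other collection of events during the 6 weeks.
- **Both arms.** The harms section adds a general clause: whether reported or observed by participants, assessors or practitioners, all "adverse events will be recorded in the sessions forms, which are stored on a secured storage". Serious adverse events go to the ethics committee, with no restriction by arm.

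Some harm-related measures are taken alike in both arms. Under Outcomes {12}, the K-SADS depressive section and its suicidality supplement are given after the intervention period. Under Trial design {8}, they are given by independent assessors blind to condition. The CDI-2 is also an outcome at T1 in both arms.

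**The concern.** The definition and the capture rule do not fit together. One arm has a weekly occasion on which events are noted and a form to note them on. The other arm has neither before T1: an event enters the record if it leads to a contact, or if someone happens to report or observe it. A passing exacerbation, or self-injury that prompts no contact, is more likely to be written down in the EMDR arm than on the waiting list.

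This matters because T0–T1 is the only randomised comparison; after T1 the waiting-list participants receive EMDR as well. If event counts from this period are later set side by side, more intensive recording and a true excess of symptom worsening would look the same. An analysis plan cannot repair this afterwards, because events that were never asked about cannot be recovered. The article presents the trial as the first of this therapy for adolescent depressive symptoms, and it has no data monitoring committee, so an interpretable harms record has real value.

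**Working it through.** The plan states no adverse-event rate and no harms calculation, so there is no figure to reproduce. The check is a comparison of the text by arm, followed by an illustration.

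**Step 1. Ascertainment over T0–T1, side by side**

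| Element | EMDR arm | Waiting-list arm |
|---|---|---|
| Scheduled occasions for noting events | up to 6, weekly | none stated |
| Arm-specific trigger | each session | contact for crisis or sudden worsening |
| Reports or observations by participants or staff | covered | covered, but no scheduled occasion before T1 |
| Form named for adverse events | session form | session form, with no sessions before T1 |
| Serious adverse events | reportable | reportable |
| K-SADS depressive section and suicidality supplement at T1 | yes, blinded assessor | yes, blinded assessor |
| CDI-2 at T1 | yes | yes |

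The first four rows differ in law or in practice; the last three do not. The instruments described under Outcomes {12} include no adverse-event checklist. Table 1 and Figure 1 could not be read in the text at hand.

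**Step 2. What the shared measures leave uncovered**

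The CDI-2 asks about the past 2 weeks. In a 6-week period, a worsening that has resolved by the end of week 4 (6 − 2 = 4) falls outside its window. Crisis contacts, and undesirable experiences other than depression and suicidality, have no equal measure in the two arms.

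**Step 3. Illustration of the direction (all rates assumed)**

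Input from the article: 64 participants allocated 1:1, so 32 per arm. Assumptions: the same true risk *p* in both arms, and detection probabilities *d*E (EMDR) and *d*W (waiting list).

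Recorded participants with an event = 32 × *p* × *d*. Apparent ratio = (32 × *p* × *d*E) / (32 × *p* × *d*W) = *d*E / *d*W. The true risk cancels.

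With *p* = 0.30, so that 32 × 0.30 = 9.6 participants per arm truly have an event:

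- *d*E = 0.9, *d*W = 0.6: 9.6 × 0.9 = 8.6 against 9.6 × 0.6 = 5.8; ratio 0.9 / 0.6 = 1.5.
- *d*E = 0.9, *d*W = 0.3: 8.6 against 9.6 × 0.3 = 2.9; ratio 0.9 / 0.3 = 3.0.
- Equal detection: ratio 1.0.

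**Step 4. Why repeated occasions favour detection**

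If one occasion picks up an event with probability *c*, and occasions are independent, *k* occasions pick it up with probability 1 − (1 − *c*)^*k*. For *k* = 6:

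- *c* = 0.2: 1 − 0.8^6 = 0.74
- *c* = 0.4: 1 − 0.6^6 = 0.95
- *c* = 0.6: 1 − 0.4^6 = 1.00 (0.996)

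A single occasion gives 0.2, 0.4 or 0.6. This treats every event as open to detection at all six sessions, which favours the EMDR arm, so it shows direction only.

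**The case against.** A reader might infer that harms cannot be compared between the arms at all. The documents do not support that. Blinded assessors apply the K-SADS depressive section and suicidality supplement to both arms at T1, the CDI-2 is completed in both, and serious adverse events are reportable in both. These comparisons stand, with the reservation that hearing of a serious event on the waiting list also depends on a contact, a report or T1.

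A reader might also infer that nothing but crisis contacts is noted on the waiting list. That is too strong. Contacts for sudden worsening count too, and the general clause takes in anything that participants, assessors or practitioners report or observe, in either arm. What remains is that this clause gives waiting-list participants no scheduled occasion before T1 and names a form that they do not yet have.

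Three further points are fair:

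- The article announces no between-arm comparison of event counts, so the bias arises only if someone makes one. Nothing in the text warns against it, however.
- The article does not describe the per-session recording as a structured enquiry, and it does not say who initiates a waiting-list contact. The contrast is between scheduled and unscheduled recording, no more.
- A condensed article may leave forms to the full protocol, and Data management {19} mentions case record forms filled in by assessors. But the article does more than stay silent: it states a rule for each arm, and the rules differ.

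Finally, a claim that EMDR would look some specific number of times more harmful has no basis in the documents. Any such multiple only restates the detection rates that were assumed.

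**Conclusion.** The point holds for non-serious adverse events. As stated, the rules give counts over the 6-week randomised period that are not ascertained alike, and placing them side by side would probably overstate events under EMDR.

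The size of the bias cannot be derived from the documents. The ratios of 1.5 and 3.0 rest on assumed detection rates and on equal true risk. The direction rests on one further assumption: that noting events at weekly sessions detects more than waiting for a contact or a spontaneous report. That is plausible but not shown.

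The point does not touch the efficacy analyses, and it does not invalidate the T1 comparison of suicidality, depressive status or serious events. It is a worthwhile improvement at low cost, not a fatal flaw.

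**What to change.** - Add one short adverse-event checklist to the T1 Qualtrics set, identical in both arms and covering the period since T0: symptom worsening, crisis contact, self-injury, suicidal behaviour, hospitalisation. Word it without reference to sessions, so that it does not reveal the allocation.
- Provide an event form that is not tied to EMDR sessions, so that a waiting-list event, or one reported to a blinded assessor, has a place in the record.
- State that any between-arm comparison of harms will rest on that checklist, the K-SADS suicidality supplement and serious adverse events.
- Report the per-session EMDR counts separately and label them as uncontrolled.

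**Cost.** A few extra items at an existing online assessment and a small amendment. The yield is limited for participants already past T1, who contribute only K-SADS, CDI-2 and serious-event data. Inclusion began in November 2020 and was expected to end in April 2023, so this may be a large share. For them, the reporting statement alone still prevents a misleading comparison and costs nothing.
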